### **7.2.8 Secondary Endpoint #8**

- Health-related quality of life (QOL).

Again, this is not a single outcome, but rather a comprehensive assessment of multiple domains of quality of life. For each of the QOL measures, data analysis will proceed in several stages. We will start by providing simple descriptive and comparative analyses of the testing strategies as randomized. A nonparametric bootstrap will be used to estimate treatment differences with 95% CIs and p-values. Because there is currently no consensus in the statistical literature about the best way to deal with the multiple comparisons problem arising from testing each individual scale at each time point separately, two complementary approaches will be employed. First, we pre-specify the angina frequency and disease perception/QOL scales from the Seattle Angina Questionnaire (SAQ) as the CAD-specific measures of primary interest, since those measures most directly quantify the therapeutic goal of coronary diagnosis and therapy, namely to minimize symptoms and optimize patients' QOL. We also specify cardiac functional status measured with the Duke Activity Status Index (DASI) as a primary QOL outcome measure of interest. Other disease-specific and generic QOL measures are therefore assigned to a secondary (descriptive) status in the analyses. Second, we will fit a mixed effects longitudinal proportional odds model that makes use of all available QOL data at each study assessment point to model the time profile (fixed effect) using a restricted cubic spline function. Using the fitted model, we can estimate the overall difference in the QOL measures as well as test the global hypothesis of no difference over time. We can also estimate the difference in the areas under the two QOL curves corresponding to the two randomized arms (and test the hypothesis of no difference on average). In addition, we will estimate differences in QOL at the end of the study or at intermediate points such as at 1 year. A separate more detailed analytic plan

for the quality of life analyses will also be developed by the EQOL Coordinating Center.

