## E6 *Quality-of-life Assessments*

Baseline QOL interviews will be administered to ~6000 subjects enrolled (prior to July 2012) by site personnel as soon as possible after consent, preferably before the subject's randomization. Completed questionnaires will be sent directly to the EQOL CC for data processing. Follow-up QOL questionnaires will be administered via structured telephone interview by DOFG trained and supervised interviewers at 6 months, 12 months, and 24 months post-randomization (among patients followed for 24 months). Proxy QOL questionnaires will be used when a subject has died in the follow-up interval or has become incapacitated; these questionnaires will include items that can be reliably obtained from a relative, caretaker, or medical record. Proxy questionnaires will be used if the subject is unable to participate in follow-ups via telephone interview.

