## **2.f Quality-of-life Analyses**

For each of the QOL measures, data analysis will proceed in several stages. We will start by providing simple descriptive and comparative analyses by intention-to-treat. A nonparametric bootstrap will be used to estimate treatment differences with 95% CIs and *P* values. Because there is currently no consensus in the statistical literature about the best way to deal with the multiple comparisons problem arising from testing each individual scale at each time point separately, we propose 2 complementary approaches. First, we will prespecify the angina frequency and disease perception/QOL scales from the SAQ as the CAD-specific measures of primary interest, since these measures most directly quantify the therapeutic goal of coronary diagnosis and therapy: to minimize symptoms and optimize patients' QOL. We will also specify cardiac functional status measured with the DASI as a primary outcome measure of interest. Other disease-specific and generic QOL measures will be assigned to a secondary

---

(descriptive) status in our analyses. Second, we will fit a mixed effect longitudinal proportional odds model that makes use of all available QOL data at each study assessment point to model the time profile (fixed effect) using a restricted cubic spline function. Using the fitted model, we can estimate the overall difference in the QOL measures as well as test the global hypothesis of no difference over time. We can also estimate the difference in the areas under the 2 QOL treatment curves (and test the hypothesis of no difference on average). In addition, we can estimate differences in QOL at the end of the study or at intermediate points such as at 1 year. Statistical power estimates for this part of our analysis show that we should have in excess of 90% power to detect  $\frac{1}{4}$  standard deviation differences in the 3 principal QOL endpoints.

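### No baseline adjustment is stated for the bootstrapped quality-of-life differences, so as written their confidence intervals are wider than the collected data allow

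*Supplement*

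**What the plan says.** SAP 7.2.8, like protocol F2 2.f, sets out the quality-of-life analysis in stages. The first: "We will start by providing simple descriptive and comparative analyses of the testing strategies as randomized". The estimator and its inference follow: "A nonparametric bootstrap will be used to estimate treatment differences with 95% CIs and p-values". Two SAQ scales (angina frequency and disease perception) and the DASI are named as the measures of main interest.

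The second approach is a mixed-effects longitudinal proportional odds model on all available quality-of-life data, with a spline for time. It yields an overall difference, a global test, an area-under-the-curve difference and differences at chosen times. The role of the baseline score in it is not described. SAP 7.2.8 closes by deferring further detail to a separate plan from the economics and quality-of-life coordinating center.

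The baseline data exist. Protocol E6: "Baseline QOL interviews will be administered to ~6000 subjects enrolled (prior to July 2012) by site personnel as soon as possible after consent", with the timing given as "preferably before the subject's randomization". Follow-up interviews are at 6, 12 and 24 months.

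On power, protocol 2.f says "we should have in excess of 90% power to detect" quarter "standard deviation differences in the 3 principal QOL endpoints".

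**The concern.** Elsewhere the SAP says so when it wants adjustment. SAP 7.1 adjusts the primary analysis for the Appendix A covariates, and SAP 7.2.1 repeats this for secondary endpoint #1. Appendix A is headed for the primary endpoint and lists no quality-of-life score. Section 7.2.8 has no such statement and calls its comparisons simple, so the natural reading is an unadjusted contrast between arms.

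If a scale correlates with its own baseline, that contrast leaves explainable variance in the standard error and chance baseline imbalance in the point estimate. What is at stake is precision on the three named scales. The trial does claim to value precision: protocol F1 counts confidence-interval width among the considerations behind the sample size, and SAP section 6 plans extensive use of intervals.

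The longitudinal model does not clearly recover the loss. If baseline enters as one more outcome with free arm means, a contrast at a single visit need not gain the precision of covariate adjustment, and an area difference starting at baseline would carry the baseline imbalance. Nor would that model change the bootstrapped intervals and p-values.

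**Working it through.** **Inputs from the documents.** About 6000 quality-of-life patients (protocol E6); 1:1 allocation (SAP section 4), hence about 3000 per arm; two-sided tests (SAP section 6); alpha 0.05, implied by the 95% intervals; target difference 0.25 SD with more than 90% power (protocol 2.f).

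**Assumed.** The correlation rho between a scale's baseline and follow-up scores is not in the documents. I use 0.3 to 0.7. Outcome SD is set to 1, with complete follow-up and usable baselines.

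**The plan's own power statement.** Patients per arm for 90% power at 0.25 SD: 2 × (1.960 + 1.282)² / 0.25² ≈ 337. With 3000 per arm the standard error is √(2/3000) = 0.0258 SD, so 0.25 SD is about 9.7 standard errors and power exceeds 99.9%. With only 1500 patients analysed in total it is still 99.8%. The statement of more than 90% holds without any baseline adjustment.

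**Unadjusted contrast, 3000 per arm.**
- 95% half-width: 1.960 × 0.0258 = 0.051 SD
- Difference detectable with 90% power: 3.242 × 0.0258 = 0.084 SD

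**Baseline-adjusted contrast (linear ANCOVA).** The residual SD is √(1 − rho²), so both quantities are multiplied by that factor. The equivalent unadjusted total is 6000 / (1 − rho²).

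| rho | factor | narrower by | half-width (SD) | detectable at 90% (SD) | equivalent total N |
|---|---|---|---|---|---|
| 0.3 | 0.954 | 4.6% | 0.048 | 0.080 | about 6,590 |
| 0.5 | 0.866 | 13.4% | 0.044 | 0.072 | 8,000 |
| 0.7 | 0.714 | 28.6% | 0.036 | 0.060 | about 11,770 |

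Bootstrapping one simulated data set per correlation (3000 per arm, 1000 resamples) gave width ratios of 0.97, 0.88 and 0.68, in line with the formula given resampling noise.

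**Fewer patients at follow-up.** The factor does not depend on the number analysed; absolute widths do. With 4000 in total the unadjusted half-width is 0.062 SD, and the adjusted one runs from 0.059 (rho 0.3) to 0.044 SD (rho 0.7).

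**Chance imbalance.** With 3000 per arm the 95% range for a baseline difference is about ±0.051 SD. It shifts the raw follow-up difference by rho times that: about 0.015 SD at rho 0.3 and 0.035 SD at rho 0.7.

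**The case against.** The strongest reply is that the plan is silent, not wrong. A bootstrap is a method of inference and is compatible with an adjusted estimate. The sentence at issue describes only the opening stage. The longitudinal model uses all available data, and baseline is a scheduled quality-of-life assessment in the protocol E2 table. How the baseline score enters each model is just what the announced separate plan would hold. This stands in part. A reader might infer that the SAP prescribes raw differences or discards the baseline; it says neither, and the documents do not support going beyond the natural reading.

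A second reply is that little depends on it. Randomization keeps the unadjusted difference unbiased, its interval already allows for chance imbalance, and power at the stated target is beyond 99.9% either way. SAP section 18 leaves quality of life out of its ordered list of pivotal results. This stands too, and rules out inferring that the quality-of-life comparison is biased or underpowered.

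Third, the gain rests on an undocumented correlation. At 0.3 it is under 5%, and the √(1 − rho²) rule is for linear adjustment, not the proportional odds model. That is right, and is why the gain is given as a range for the bootstrapped contrast only.

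Finally, E6 only prefers a pre-randomization interview, and protocol E2 places the questionnaires at the time of randomization. Adjustment that simply dropped patients with late or missing baselines would conflict with SAP section 5, which analyses all randomized subjects. The fix has to provide for them.

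**Conclusion.** The point holds as a free gain in precision that the plan does not claim. SAP 7.2.8 and protocol 2.f commit to bootstrapped differences with intervals and p-values, state no baseline adjustment, and do not say how baseline enters the longitudinal model. For linear adjustment with about 3000 per arm, complete data and rho between 0.3 and 0.7, intervals would be about 5% to 29% narrower, and the difference detectable with 90% power would be 0.080 to 0.060 SD instead of 0.084 SD. The validity of the unadjusted contrast and the protocol's power statement are not in question. If the separate quality-of-life plan already specifies adjustment, SAP 7.2.8 needs only a cross-reference to it.

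**What to change.** In SAP 7.2.8, or in the separate quality-of-life plan with a pointer from 7.2.8, state that:

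- each bootstrapped difference is the arm effect from a regression of the follow-up score on arm, the same scale's baseline score and the pre-randomization choice of functional test, resampling patients and refitting each time. Including the functional-test choice follows Appendix A's own reason for including it in the primary model;
- the longitudinal model either takes baseline as a covariate or treats it as an outcome with means constrained equal across arms;
- only scores obtained before randomization count as baseline;
- patients with a missing or post-randomization baseline stay in, for example by mean imputation with an indicator (whether a score was in hand at randomization is fixed before assignment), or through the constrained longitudinal model.

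The cost is a short paragraph and some programming, plus a check of interview dates against randomization dates. No new data are needed. It should be fixed before outcomes are compared by arm, so that the adjustment is prespecified.

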## 8. Subgroup Analyses

An assessment will be made as to whether the effect (if any) of testing strategy is similar for all patients, or whether it varies according to specific patient characteristics. In particular, these analyses will focus on whether the relative effect of testing strategy differs according to the following baseline variables:

- Age (<65 years vs.  $\geq 65$  years)
- Gender (Male vs. Female)
- Race (White vs. Non-white)
- Baseline pre-test assessment of the risk of significant epicardial stenosis ( $\geq 70\%$ ) or left main stenosis  $\geq 50\%$  as assessed by the site investigator [low risk ( $\leq 30\%$  likelihood), intermediate risk (31-70% likelihood), and high risk ( $> 70\%$  likelihood)]
- Coronary disease risk equivalent (history of either diabetes, cerebrovascular disease, or peripheral artery disease) vs. none of these factors
- Characteristics of the precipitating symptoms (Angina type classification—typical, atypical or non-anginal pain), as reported for each patient by the enrolling site
- Combined Diamond-Forrester and CASS score indicating the pre-test likelihood of underlying CAD, categorized as low (<10%), intermediate (10-90%, and high (>90%)
- Pre-randomization choice of the functional test to be used if the subject was randomized to the functional testing arm. Specification of this choice was required of the site investigator prior to randomization and was built into the randomization scheme as a stratification factor to ensure that the benefits of randomization in this subgroup comparison were maintained.

These analyses will utilize the Cox model and will be accomplished by testing for interactions between the randomized testing strategy and these specific baseline variables. In addition to the formal assessment of the randomized testing strategy by covariate interactions, effects of the diagnostic testing strategy characterized by a hazard ratio and 95% confidence interval will be calculated and displayed using a forest plot for the subgroups of subjects defined by the variables listed above. These descriptive hazard ratios will be carefully interpreted in conjunction with the formal interaction tests.

The effect of diagnostic testing strategy may also be examined in other subgroups of clinical interest (in addition to those listed above).

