### ***Anatomic Testing Arm: CTA***

Because CTA is quick, robust, readily available, and accurate, it may lead to a major practice shift in the evaluation of chest pain where a strategy of imaging coronary anatomy is preferred over the current practice of first searching for inducible ischemia using functional testing. In this sense its widespread adoption would represent substantial change, as it may improve diagnostic testing in an unexpected way (through anatomic rather than functional information) and may alter the indications for testing, thereby expanding the patient population being tested. Further, there is evidence of increasing physician confidence over time, a hallmark of an improved diagnostic testing strategy. This growing experience indicates that the greatest strength of CTA may lie in excluding obstructive CAD in lower-prevalence cohorts—exactly the symptomatic population being studied in PROMISE. Finally, because of its visual strength, CTA has an inherent important motivational ability that has been shown to improve prescription and adherence to effective preventive strategies, an important goal of any testing strategy. On the other hand, CTA cannot be performed in all patients, as calcified lesions and temporal and spatial resolution can be limiting. However, evidence suggests that CTA is superior to functional testing in reducing false-positive and false-negative test results, identifying nonobstructive disease, improving the prognostic accuracy of a negative test, and extending the “warranty period” of test results, all of which strongly suggest clinical superiority over functional testing.

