## **16. Broader Assessment of Prognostic Factors**

With the large database of information that will be collected on the 10,000 subjects enrolled in this study, extensive regression modeling analyses will be performed that goes beyond a prognostic assessment of the test results. These analyses will use primarily the Cox regression model to identify and assess the factors (predictors) that are associated with the clinical outcomes of these subjects. These analyses will comprehensively evaluate the strength and shape of the relationships of numerous baseline clinical factors with the clinical outcomes, in addition to characterizing the prognostic relationships of the measures that arise from the diagnostic tests. The incremental prognostic value of test results over traditional clinical descriptors will be of particular interest.

For continuous clinical variables, we will examine the relationships between individual variables and major clinical outcomes using a flexible model-fitting approach involving restricted cubic spline functions (cubic polynomials). These functions will be graphically and statistically examined to assess the linearity of the relationship with the log hazard ratio. Where relations are nonlinear, the shape will be characterized either using spline functions or an appropriate transformation of the data. We will also examine whether the prognostic relationship of any important predictor variable differs for particular levels of other important descriptors by testing for interactions among the prognostic clinical variables. While these analyses are more exploratory than the rigorous pre-specified primary and secondary comparisons of the randomized arms of the trial, they will nonetheless be helpful in elucidating relationships and identifying the key factors that impact patient outcomes and any observed differences in outcomes between the diagnostic testing arms. Separate analysis plans will be prepared that will pre-specify all of the various steps of the modeling process including the specific set(s) of variables that will be considered, the specific outcomes of interest, the approach to model development and validation, and the

assessment of the predictive performance of the resulting statistical model(s) and any prognostic score(s) developed from the analyses.

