## Appendix A

### **List of covariates to be included in the primary endpoint analysis:**

- Age
- Sex
- Coronary disease risk equivalent (history of either diabetes, cerebrovascular disease (CVD), or peripheral artery disease (PAD))

In addition, the stratification factor used in the randomization, namely the choice of the functional test to be used if the patient was randomized to the functional testing strategy, will be included as a covariate. This particular factor is included to preserve consistency in the analysis with the stratification used in the randomization, and not because it is expected to be prognostic.

Cerebrovascular disease (CVD) will be considered present if the patient has a history of any of the following: stroke, TIA, carotid artery stenosis  $\geq 50\%$ , or history of carotid revascularization.

Age will be included in the Cox model analysis as a continuous variable, modeled linearly (i.e., assuming linearity in terms of the log hazard ratio).

Every effort will be made to have complete data for each of these variables in 100% of the randomized patients. Despite these vigorous efforts, if the information on CVD or PAD is missing for any patient, it will be assumed that those conditions are absent. It is expected that data will be complete for the other variables listed above.

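### SAP section 8 tests effect modification by age and by Diamond-Forrester/CASS likelihood on cut variables only, which loses power if the CTA effect changes gradually along those scales

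*Supplement*

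**What the plan says.** SAP section 8 asks whether the relative effect of testing strategy differs across a list of baseline variables. Three of them are numeric quantities that enter as classes:

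- Age, in two classes: "Age (<65 years vs" 65 and over.
- The combined Diamond-Forrester/CASS score, in three classes: "indicating the pre-test likelihood of underlying CAD, categorized as low (<10%), intermediate (10-90%, and high (>90" percent.
- The site investigator's own estimate, "Baseline pre-test assessment of the risk of significant epicardial stenosis", in three classes with cuts at 30% and 70%.

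The method is a Cox model, "testing for interactions between the randomized testing strategy and these specific baseline variables". Hazard ratios by class are shown in a forest plot and are to be read together with those tests.

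Elsewhere the SAP does use continuous scales, but for other purposes. Appendix A, on the adjustment covariates of the primary analysis, states: "Age will be included in the Cox model analysis as a continuous variable, modeled linearly". Section 16, on prognostic modelling, plans a "flexible model-fitting approach involving restricted cubic spline functions". Neither is an interaction with randomized strategy.

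Protocol Amendment 2, F2 section 2.a, names age for the interaction assessment without giving a cut. F1 lists the examination of subgroups, including age and cardiovascular risk factors, among the reasons for the sample size, but states no power for any interaction test.

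**The concern.** A cut treats everyone within a class as alike. On the Diamond-Forrester/CASS score, a patient at 15% and one at 85% fall in the same class, and only contrasts with the two extreme classes inform the test. On age, 46 and 64 are the same and 64 and 66 differ. If the CTA effect shifts gradually along either scale, the interaction test discards the within-class part of the signal.

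The question matters in this trial. Section C5 of the protocol suggests that "the greatest strength of CTA may lie in excluding obstructive CAD in lower-prevalence cohorts", so whether the effect on outcomes depends on pre-test likelihood is a natural question for readers deciding whom to send for CTA. A weakened test makes it more likely that a true gradient goes undetected. Since the SAP accepts linear age in its primary model and splines in its prognostic models, the tools for a fuller test are already in the plan.

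**Working it through.** **1. The plan's own power figure.** F1 gives no interaction power, so the overall figure is reproduced to confirm the framework. Schoenfeld's formula, 1:1 allocation, two-sided 0.05: power = Φ(√D/2 × |ln HR| − 1.96). Events come from exponential hazards with follow-up uniform on 2 to 4 years (the original timetable of 24 months' accrual and at least 24 months' follow-up), HR 0.80 and no loss.

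- 8% rate at 2.5 years: D = 859, power 90.5% (F1: above 90%).
- 6% rate: D = 645, power 80.9% (F1: 80%).

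**2. Events for the interaction tests.** 9% versus 7.2% at 2.5 years, 5,000 per arm, 3% loss.

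- At 2.5 years: 5,000 × (0.09 + 0.072) × 0.97 = 786.
- At 2 years, the average follow-up in the SAP: about 634.

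**3. Formula.** For a 1:1 trial the interaction test has noncentrality λ = (D/4) × δ² × R². Here δ is the change in log hazard ratio per SD of the covariate. R² is the share of covariate variance kept by the classes (1 if continuous). The test has 1 df for a continuous or two-class variable and 2 df for three classes. The SAP states no alpha for interactions; 0.05 two-sided is assumed.

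To give the continuous test 80% power, λ = (1.96 + 0.84)² = 7.85. That means a hazard-ratio ratio per SD of exp(√(4 × 7.85/786)) = 1.22 with 786 events, or 1.25 with 634.

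**4. Age cut at 65.** For a roughly normal covariate with a share p above the cut, R² = φ(z)²/[p(1 − p)]. The share aged 65 or over is not in the documents; 25-50% is assumed.

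- p = 0.50: 0.399²/0.25 = 0.64; λ = 5.00; power 61%.
- p = 0.25: 0.318²/0.1875 = 0.54; λ = 4.23; power 54%.

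So 36-46% of the information is lost. A simulation (600 runs per setting, about 804 events, age mean 59-64 and SD 8 assumed) gave 79-82% for continuous age and 60-66% for the cut.

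**5. Likelihood in three classes.** The share between 10% and 90% is not given; 80-95% is assumed. For a symmetric normal shape with a share t in each tail, R² = 2φ(z)²/t.

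- 80% in the middle: 2 × 0.1755²/0.10 = 0.62; λ = 4.84 on 2 df; power 49%.
- 95% in the middle: 2 × 0.0584²/0.025 = 0.27; λ = 2.14; power 24%.

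Allowing for other shapes, R² runs from about 0.18 to 0.64 and power from about 17% (λ = 1.41) to 51% (λ = 5.02). With 98% in the middle class, power is 10-15%.

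**6. Fixed gradients, 634 events.** Power of each test:

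| HR ratio per SD | Continuous | Age cut | Likelihood classes |
|---|---|---|---|
| 1.15 | 42% | 25-29% | 9-22% |
| 1.20 | 63% | 39-45% | 13-36% |
| 1.25 | 80% | 54-61% | 17-51% |
| 1.30 | 91% | 68-75% | 22-65% |

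**The case against.** The strongest reply is that the gain depends on the shape assumed. If the effect stepped exactly at 65, the cut test would lose nothing and a linear test would be the one keeping only 54-64% of the information. This stands: the advantage of the continuous scale is conditional on a gradual, roughly monotone change. C5 concerns the ability to rule out disease and does not establish such a gradient in event hazard. The score's distribution is also unknown, as is whether it is smooth or takes a limited set of values.

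Second, pre-test likelihood is looked at in another way. The site-assessed likelihood, cut at 30% and 70%, divides the broad middle band, so it would be wrong to infer that the plan cannot separate a 15% patient from an 85% one. This also stands, though it is a different measure and is itself categorised.

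Third, the analysis is supportive. F1 promises only a prudent look at subgroups, and SAP section 18 leaves them out of the ordered interpretation. The continuous test is no cure either: at a hazard-ratio ratio of 1.15 per SD and 634 events it has 42% power.

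Two stronger readings are not supported. One is that a non-significant interaction would decide how the forest plot is read, or be reported as a uniform effect; section 8 says only that the two are interpreted together. The other is that the 10% and 90% cuts lack a source. The score carries citations, one of them a guideline, and what it says cannot be checked here. A conventional cut can in any case define forest-plot rows without defining the test.

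**Conclusion.** The point holds in a limited form. Section 8 bases the interaction tests for age and the Diamond-Forrester/CASS likelihood on classes, and no continuous interaction is planned anywhere in the SAP. Given a roughly linear log hazard ratio and the assumed distributions, the age test falls from 80% power to about 54-61% and the likelihood test to about 17-51%. The direction is secure for any gradual monotone change spread over the scale; the size is not, because the documents supply neither distribution. No primary or key secondary estimate, error rate or conclusion is affected. It is a worthwhile, low-cost improvement to a supportive analysis.

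**What to change.** In SAP section 8, state that the interaction p-value for age comes from strategy by continuous age, linear as in Appendix A. For the Diamond-Forrester/CASS likelihood, take it from strategy by continuous likelihood, naming in advance either a linear term or a 3-knot restricted cubic spline. Plot the estimated hazard ratio with its 95% confidence interval across each scale. Keep the existing classes as descriptive rows of the forest plot.

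The cost is two sentences and two model terms. Age is collected, and the likelihood must be computed before it can be cut. The primary analysis and its alpha do not change. The downside is reliance on an assumed functional form, which the spline (at the price of one further degree of freedom) and the retained class estimates help to check. Fixing the form in advance also avoids a choice made after seeing the data.
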